## Abstract

**Background: **75% of all mental health problems have their onset before the end of adolescence. Therefore, adolescence may be a particularly sensitive time period for preventing mental health problems. Affective control, the capacity to engage with goal relevant and inhibit distracting information in affective contexts, has been proposed as a potential target for prevention. In this study, we will explore the impact of improving adolescents’ affective control capacity on their mental health.

**Methods: **The proof-of-principle double-blind randomized controlled trial will compare the effectiveness of an app-based affective control training (AffeCT) to a placebo training (P-Training) app. In total, 200 (~50% females) adolescents (11-19 years) will train for 14 days on their training app. The AffeCT will include three different
*n*-back tasks: visuospatial, auditory and dual (i.e., including both modalities). These tasks require participants to flexibly engage and disengage with affective and neutral stimuli (i.e., faces and words). The P-Training will present participants with a perceptual matching task. The three versions of the P-Training tasks vary in the stimuli included (i.e., shapes, words and faces). The two training groups will be compared on gains in affective control, mental health, emotion regulation and self-regulation, immediately after training, one month and one year after training.

**Discussion: **If, as predicted, the proposed study finds that AffeCT successfully improves affective control in adolescents, there would be significant potential benefits to adolescent mental health. As a free app, the training would also be scalable and easy to disseminate across a wide range of settings.

**Trial registration: **The trial was registered on December 10th 2018 with the International Standard Randomised Controlled Trial Number (Registration number:
ISRCTN17213032).

## Abbreviations

AffeCT = Affective control training; P-Training = Placebo training; DERS = Difficulties in Emotion Regulation Scale

## Background

75% of all mental health problems have their onset before the end of adolescence
^1^. Many of these disorders, for example major depressive disorder, will be recurrent throughout the lifespan creating large costs in human suffering
^2–
4^. Adolescence – here defined as starting with puberty and ending with the attainment of an independent adult role (10–24 years
^5^) – thus may be a particularly sensitive time period for prevention of mental health problems
^6^. In this study, we will explore the impact of improving adolescents’ affective control capacity on their mental health.

Affective control, the capacity to flexibly engage and disengage from affective information as required by current goal-demands, is impaired across a wide range of mental health problems
^7^. Poor affective control capacity has been shown to be associated with poor mental health outcomes over and above neutral ‘cool’ cognitive control during adolescence
^8–
12^. We have previously suggested that this association between affective control and mental health can be partially accounted for by emotion regulation
^12^. That is, affective control constitutes the cognitive building blocks of successful emotion regulation. Emotion regulation refers to the automatic and volitional processes deployed to modify an individual’s affective experiences
^13^. Improving affective control in adolescents, whose everyday environments can include high levels of negative affect and affective fluctuations
^14–
17^, may then confer benefits to emotion regulation capacity and mental health.

Studies conducted in adults have shown that training affective control leads to improvements in both emotion regulation capacity and self-reported mental health
^18–
21^. Cool cognitive control training has also been shown to be effective in reducing symptoms of depression and anxiety, as well as improving emotion regulation
^22–
27^.

The cognitive training literature in children and adolescents has largely focused on remediation for learning difficulties as well as neurodevelopmental disorders such as attention deficit and hyperactivity disorder (ADHD
^28,
29^). Less is known about the impact of cognitive control training on young people’s mental health
^30^. A notable exception is the literature on cognitive training for adolescents with psychotic symptoms
^31,
32^, which synthesizing evidence suggests shows promising effects on symptoms and functioning
^33^. However, given that affective control in particular may be impaired in adolescents with high levels of mental health problems, we will trial the effect of an affective control training (AffeCT) paradigm in our forthcoming study. Specifically, we will explore whether AffeCT improves adolescents’ mental health and emotion regulation capacity and whether the magnitude of these improvements differs as a function of age.

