### The present study

To investigate the potential of AffeCT in adolescents, the current study will include 200 adolescents (11–19 years). Including this age range will allow us to investigate the potential age-related differences in the effectiveness of training, as shown in studies using cool cognitive training paradigms
^34^.

The training that will be used in the current study is a variant of a paradigm we applied successfully in adults and a preliminary study in adolescents with posttraumatic stress disorder
^21,
35,
36^. The impact of the AffeCT will be assessed in a proof-of-principle double-blind randomized controlled trial. In the AffeCT, participants will be presented with visuospatial, auditory and dual (combined visuospatial and auditory) versions of the
*n*-back task. The three versions will, respectively, require participants to continuously update faces or words or both. On the first three days of the 14-day training programme, participants will train on one version each day. On days 4–14, participants are free to select any or all of the training versions. However, both training groups will be provided with a rationale suggesting that training on version C is likely to confer more benefits than the other two versions. By providing a rationale for one training being associated with superior benefits compared to others, participants should be motivated to select C over the other two training versions. However, C is more cognitively demanding, therefore requiring self-regulation to engage in this task over the others for potential future benefits. We hypothesise that opting to engage in a more challenging but potentially more beneficial task is an index of self-regulation, which has been shown to be associated with mental health across the lifespan
^37^. This will allow us to explore the role of self-regulation in cognitive training and any effects on mental health outcomes.

The tasks train affective control by requiring effective engagement and disengagement with affective information depending on task-demands. Affective valence is introduced to the training by including valenced stimuli. Specifically, the AffeCT will include 20% neutral, 20% positive and 60% negative stimuli. The rationale for including stimuli of different valences is that mental health problems can be characterised by difficulties disengaging from negative material
^38^, avoidance of negative (e.g., threatening) information

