*n*-back task across the two training groups.2. AffeCT compared to P-Training will lead to greater improvements in all facets of affective control as measured by non-trained affective control tasks, including affective inhibition, updating and shifting tasks (
*affective control facets hypothesis*).3. The benefits of AffeCT will vary as a function of age (
*age-related change hypothesis*).4. Increases in affective control from pre- to post-training will be associated with fewer self-reported mental health problems and emotion regulation difficulties, as well as higher levels of self-reported self-control, at each assessment time point (
*mental health hypothesis*).

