**Figure 1. f1:**

Study timeline. T1 – T4 = Assessment time point 1 – 4; A/B/C = refers to the three different versions of the training tasks available in both training groups; Pre- and post-training assessment = Assessment sessions run prior to and after completing the training phase; Training phase = period of training on the app; 1-month and 1-year online follow up assessment = key outcomes will be assessed online one month and one year following the completion of the training.

***Training phase.*** During the training phase, participants from both training groups will be presented with three different training tasks (see below for descriptions). On the first three days they will complete a different version of the training task each day. The presentation order of the three versions will be fixed for days 1–3. The P-Training group will complete the shapes (A), words (B), and faces (C) versions on the first, second, and third day of training, respectively. The AffeCT group will complete the visuospatial (A), auditory (B), and dual (i.e., including both modalities; C) versions of the training task on the first three days of training. From the fourth day of training onward participants in both groups will be free to select any of the three different versions of their training schedule.

At the beginning of the training, both groups will be told that they should spend as much time as possible training on version C due to its benefits to attention, memory and emotion regulation. Version C in the AffeCT will be significantly more cognitively demanding
^45^ than A and B, whereas there are no differences in cognitive demands between versions A, B or C in the P-Training. Emulating the design of established measures of academic diligence and self-regulation
^46–
48^, the ratio of time spent training on version C relative to A and B will be taken as a behavioural index of self-regulation.

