**Figure 4. f4:**
[figure not shown]
Predicted structure of affective and cognitive functioning at baseline. The figure offers a schematic representation of the predicted structure of cognitive and affective control in adolescents. Raven’s i1 – 12 = items 1 – 12 on the Raven’s Advanced Progressive Matrices; d’ = d prime on backward digit span; RT = reaction time; rE = proportion random errors; Acc = percentage trials correct. Rectangular boxes = measured variables; ovals = latent constructs.

To investigate the first hypothesis (
*affective control training hypothesis*) we will use mixed effects modelling with training group as fixed effect and time as within-subject effect. The outcome of interest will be
*d*’ achieved on the affective
*n*-back task. Additionally, we will explore the impact of training on reaction time as a secondary outcome of interest. For the secondary analyses to be considered significant, we will apply a Bonferroni correction to reduce the threshold for statistical significance for two comparisons (accuracy and reaction) to α ≤ .025. We will then explore whether any effects of group and time are moderated by total training time (mins), total number of individual training sessions and ratio of time spent training on training task C relative to A and B. We plan to include these overlapping measures separately as they arguably provide different types of information. Specifically, total training time will allow us to explore dose-response relationships. The other two measures, we propose, index more motivational factors such as diligence and/or motivation by the monetary incentive. To facilitate interpretation of any potential moderating effect, we will use a SEM trees approach to these moderators and enter the relevant groupings as moderators. We will additionally investigate the effect of time spent on each training version separately on the outcome of interest and compare the effect of time spent on the single versions versus time spent on the dual version.

Our second hypothesis (

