*affective control facets hypothesis*), that AffeCT will improve inhibition, updating and shifting, will be tested with a multivariate mixed effects model. Time and group will be included as fixed effects and the three measures of affective control as outcomes of interest (i.e., working memory updating, inhibition, and set-shifting). The primary outcome of interest is accuracy, as this has been shown to be a more sensitive than reaction time in dissociating between individuals with and without mental health problems
^7^. As with the first hypothesis, we will investigate whether any training benefits are moderated by total training time (mins), total number of individual training sessions or time spent training on task C relative to A and B. The analyses will be repeated with reaction time as a secondary outcome of interest.

Our
*age-related change hypothesis*, will be tested by including age a moderator in the multivariate mixed effects model used to test the
*affective control training hypothesis*. The potentially moderating effect of age will be investigated using SEM trees. SEM trees identify age groupings to the benefits conferred by training. While the exploration is data-driven, it is theoretically informed by the literature showing differential effects of cognitive training on young compared to older adolescents
^34^. A second exploratory analysis will include age as a continuous variable in the same model to investigate any linear or polynomial effects of age.

Fourth, to test the
*mental health hypothesis,* we will use latent change score models, a subclass of SEM approaches
^77^, which naturally allows for the integration of predictors of rates of change (e.g. improvements in mental health). Specifically, we will investigate whether pre- to post-training changes in the affective control factor established at baseline are associated with fewer self-reported mental health problems and emotion regulation difficulties, as well as higher levels of self-reported self-control at each assessment time point. The primary analyses will include the post-training and one-month follow-up assessment. Secondary analyses will include the one-year follow-up.

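### The Background aims to explore whether mental-health and emotion-regulation gains differ by age, but the only age analysis uses task scores, and the one mental-health analysis names neither age nor training group

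*Protocol article*

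**What the plan says.** **Aim.** The last paragraph of the Background reads "we will explore whether AffeCT improves adolescents’ mental health and emotion regulation capacity" and continues with "whether the magnitude of these improvements differs as a function of age". The improvements referred to are those in mental health and emotion regulation.

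**Hypothesis.** The list in The present study turns this into the third hypothesis (H3), "The benefits of AffeCT will vary as a function of age", without naming an outcome.

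**Analysis of age.** In Statistical analyses, H3 is to be "tested by including age a moderator in the multivariate mixed effects model used to test the" affective control training hypothesis, that is, the first hypothesis (H1). Age enters first through SEM trees and then as a continuous variable in the same model. The H1 outcome is d' "achieved on the affective" n-back task, with reaction time secondary. The second hypothesis (H2) has a multivariate model for inhibition, updating and shifting.

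**Analysis of mental health.** H4 uses latent change score models. It relates pre- to post-training change in the affective control factor to self-reported mental health problems, emotion regulation difficulties and self-control. T2 and T3 are primary and T4 is secondary. No age or training-group term is named.

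**Self-regulation.** The present study says the free choice of training version "This will allow us to explore the role of self-regulation in cognitive training and any effects on mental health outcomes". Under Training procedure and timeline, "the ratio of time spent training on version C relative to A and B will be taken as a behavioural index of self-regulation". That ratio is a moderator in H1 and H2.

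**The concern.** The stated question and the stated model have different outcomes. An age pattern in n-back or facet scores does not show whether symptom or emotion-regulation benefit varies with age, since the two can follow different age patterns. Age is central to the design: it motivates the 11 to 19 year range, and both recruitment and randomisation are stratified by it. If the plan is followed, the age question posed in the Background goes unanswered. If an age-by-mental-health analysis is added once results are known, it will be post hoc.

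A more basic gap lies underneath. The Abstract says the two groups will be compared on gains in mental health and emotion regulation, yet no group x time model for those outcomes is stated. An age interaction therefore has no base model to attach to.

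**Working it through.** **Step 1. Trace each question to a model.**

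| Question | Stated model |
|---|---|
| Task performance by age | H3 |
| Task performance by C ratio | H1 and H2 |
| Mental health or emotion regulation by age | none |
| Mental health or emotion regulation by C ratio | none |
| Mental health or emotion regulation by training group | none |

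H3 calls its model multivariate but points to H1, which has a single primary outcome; the multivariate model is the one for H2. The ambiguity does not affect the point, because the outcomes are task measures under both readings.

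**Step 2. The plan's own power figure.** Participants gives at least 93% power for H1 with 100 per group and d = 0.40. With two-sided alpha 0.05 (assumed), power = Φ(d / (s·√(2/n)) − 1.96).
- s = 1: 0.40/0.1414 = 2.83, so Φ(0.87) = 80.7%.
- Change scores, s = √(2(1−r)), r = 0.66: s = 0.825, 0.40/0.1166 = 3.43, so Φ(1.47) = 92.9%.

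The stated figure is reachable with a pre-post correlation near 0.66. The article gives no correlation or variance components, so the figure is neither confirmed nor refuted. It concerns H1 only and does not bear on the mismatch.

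**Step 3. What an added age analysis could detect.** Regress T1-T2 change on group, standardised age and their product. Inputs: N = 200 (Participants), with all participants analysed (assumed). Allocation is 1:1, so the variance of the group indicator is 0.25. The T1-T2 correlation rho is assumed to be 0.5 to 0.8, with equal SDs at both times. Then

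SE = √(2(1−rho)) / √(200 × 0.25), and the slope detectable with 80% power at two-sided 5% is (1.96 + 0.84) × SE = 2.8 × SE.

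| rho | √(2(1−rho)) | SE (divide by 7.071) | 2.8 × SE |
|---|---|---|---|
| 0.5 | 1.000 | 0.1414 | 0.396 |
| 0.66 | 0.825 | 0.1166 | 0.327 |
| 0.8 | 0.632 | 0.0894 | 0.250 |

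Units are outcome SDs of benefit per SD of age. If only a fraction f of the 200 is analysed, each value is divided by √f.

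For scale, suppose the mean benefit were 0.40 SD, borrowing the figure planned for the n-back. A slope of 0.25 would mean 0.15 at one SD of age to one side of the mean and 0.65 at one SD to the other. A slope of 0.40 would mean 0 and 0.80. Only strong moderation would be detected reliably.

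**The case against.** **It is one introductory clause.** The Background says explore, H3 speaks only of benefits, and neither the Abstract nor the Conclusions promises an age-specific mental-health result. This stands as a limit on severity, and it makes narrowing the wording an acceptable remedy. It does not remove the mismatch, because an exploratory aim still needs an analysis.

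**The detail may sit in an analysis plan that is not shown.** This would hold if the article had left the H3 outcome open. It instead ties H3 to a named model with task outcomes. The article does note that latent change score models accommodate predictors of change, so age could be added to H4, but the only predictor it names is change in affective control.

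**The added models would be imprecise.** This stands. It is the reason to report estimates with intervals and to make no confirmatory claim. Follow-up at T3 and T4 is online, and attrition or weaker correlation there could make precision worse.

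**Stronger readings.** A reader might infer that the article promises to test whether mental-health benefit is moderated by self-regulation and then omits that test. The text does not support this. It says only that the design allows the team to "explore the role of self-regulation in cognitive training and any effects on mental health outcomes", which describes a role and is open in its grammar. The C ratio is analysed for task outcomes in H1 and H2, and self-reported self-control is an H4 outcome. A reader might also infer that the authors intend to use age effects on task scores as evidence about mental health; no passage plans that inference.

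**Conclusion.** The concern holds for age. The aim refers to mental health and emotion regulation, the age model refers to task performance, and H4 names neither age nor training group, so the plan as written yields no estimate for this aim. The conclusion rests on the text and on no calculation. The article should be corrected, but the issue does not threaten the primary comparison on n-back performance.

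The calculation bears only on what the remedy can deliver: about 0.25 to 0.40 SD per SD of age at 80% power, given 200 analysed and an assumed correlation of 0.5 to 0.8, with larger differences needed under attrition.

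The self-regulation point is minor. The C ratio arises after randomisation, and version C is more demanding than A and B only in AffeCT, so the ratio does not mean the same thing in the two groups. That limits what a C-ratio analysis of mental-health outcomes could show.

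**What to change.** 1. State a group x time model for SDQ total difficulties and DERS total at T2 and T3, with T4 secondary. This also supplies the group comparison announced in the Abstract.
2. Add group x time x continuous age to that model. Label it exploratory and report the estimate with its confidence interval.
3. Alternatively, narrow the Background sentence and the H3 conclusions to task performance.
4. Name the model H3 uses, since multivariate describes H2 and the cross-reference is to H1.
5. If the C ratio is related to mental-health outcomes, confine that analysis to AffeCT or label it non-causal. The T1 Brief Self-Control Scale can be an optional additional baseline moderator. It should not replace the C ratio, because it answers a different question from the choice of version C.

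The cost is a few models on measures already scheduled, and the small downside is more exploratory tests. At this protocol version, Trial status reports 64 participants with pre-training assessments and none with completed training or post-training assessments, so either remedy could be made before outcome data exist.

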### The present study

To investigate the potential of AffeCT in adolescents, the current study will include 200 adolescents (11–19 years). Including this age range will allow us to investigate the potential age-related differences in the effectiveness of training, as shown in studies using cool cognitive training paradigms
^34^.

The training that will be used in the current study is a variant of a paradigm we applied successfully in adults and a preliminary study in adolescents with posttraumatic stress disorder
^21,
35,
36^. The impact of the AffeCT will be assessed in a proof-of-principle double-blind randomized controlled trial. In the AffeCT, participants will be presented with visuospatial, auditory and dual (combined visuospatial and auditory) versions of the
*n*-back task. The three versions will, respectively, require participants to continuously update faces or words or both. On the first three days of the 14-day training programme, participants will train on one version each day. On days 4–14, participants are free to select any or all of the training versions. However, both training groups will be provided with a rationale suggesting that training on version C is likely to confer more benefits than the other two versions. By providing a rationale for one training being associated with superior benefits compared to others, participants should be motivated to select C over the other two training versions. However, C is more cognitively demanding, therefore requiring self-regulation to engage in this task over the others for potential future benefits. We hypothesise that opting to engage in a more challenging but potentially more beneficial task is an index of self-regulation, which has been shown to be associated with mental health across the lifespan
^37^. This will allow us to explore the role of self-regulation in cognitive training and any effects on mental health outcomes.

The tasks train affective control by requiring effective engagement and disengagement with affective information depending on task-demands. Affective valence is introduced to the training by including valenced stimuli. Specifically, the AffeCT will include 20% neutral, 20% positive and 60% negative stimuli. The rationale for including stimuli of different valences is that mental health problems can be characterised by difficulties disengaging from negative material
^38^, avoidance of negative (e.g., threatening) information
^39^ or aberrant processing of positive information
^40^. Moreover, we have recently shown in a meta-analysis that, individuals with mental health problems, affective control, measured with working memory tasks such as the training task, is similar across positive and negative valence
^7^.

The effectiveness of the AffeCT will be compared with an active placebo training (P-Training), which includes three versions: shapes, words and faces from a feature match task. The P-Training requires participants to indicate whether the items presented in two panels are matched or mismatched. The training was designed to be minimally demanding on cognitive control, while exposing participants to the same stimuli as the AffeCT.

To investigate potential benefits of the AffeCT on mental health or emotion regulation, participants will complete self-report measures immediately after training, after one month, and after one year. Additionally, the three facets of affective control –
*inhibiting* attention and responses toward goal-irrelevant affective information,
*updating* affective information or updating information in the context of affective distraction, and
*shifting* flexibly between affective and non-affective task demands – will be assessed using experimental paradigms. Inhibition will be assessed with a modified version of Preston and Stansfield’s
^41^ affective Stroop task, which requires participants to categorize adjectives as either happy or sad that are superimposed over task-irrelevant faces that are either congruent, incongruent or neutral (i.e., scrambled). Updating will be assessed with the affective digit backward span task. In this task digits are serially presented over either a neutral or affective background image and then recalled in reverse order (modified version of standard digit span task;
42). Finally, shifting will be assessed with an affective card sorting task, which requires participants to flexibly switch between affective and neutral sorting rules
^12^.

This study will allow us to investigate the following four hypotheses:

1. Affective control can be improved in adolescents (
*affective control training hypothesis*). To investigate this hypothesis, we will compare individuals’ performances on the affective
*n*-back task across the two training groups.2. AffeCT compared to P-Training will lead to greater improvements in all facets of affective control as measured by non-trained affective control tasks, including affective inhibition, updating and shifting tasks (
*affective control facets hypothesis*).3. The benefits of AffeCT will vary as a function of age (
*age-related change hypothesis*).4. Increases in affective control from pre- to post-training will be associated with fewer self-reported mental health problems and emotion regulation difficulties, as well as higher levels of self-reported self-control, at each assessment time point (
*mental health hypothesis*).

